### Inclusion and exclusion criteria

A hospital was eligible for the trial if it had a functional operating room and had performed at least 200 caesareans in 2012. Twenty-two public hospitals were included in the trial between May and June 2014, out of a total of 24 eligible hospitals (91.6 %). Two university hospitals were excluded due to the high number of personnel in training. The 22 hospitals in the trial are representative of Burkina Faso’s current health system, spanning the full range in terms of context (urban versus rural), level of care (district and regional hospitals) and qualifications of health personnel. This process thus guaranteed a certain external validity of the results.

The intervention directly targets health professionals who provide obstetric care in the participating hospitals, while indirectly targeting the women giving birth there. The health professionals have been trained in the management of labour and delivery, with some also trained to perform caesareans. All health professionals involved in managing deliveries in their institutions were included in the study (*n* = 978). This total consisted of obstetricians and gynaecologists (*n* = 39), general practitioners (*n* = 32), physician anaesthetists (*n* = 3), nurses (*n* = 463), and midwives (*n* = 441). Maternity services personnel who were not involved in obstetric care in the labour room were excluded from the trial (*n* = 446).

The first 100 women with caesarean deliveries in the 22 hospitals during a 6-month period in the year preceding the intervention (May 2 to November 2, 2014) were included in the study. The first 100 women with caesarean deliveries in the 6 months following the end of the intervention will also be included. As the intervention will last 1 year, the pre- and post-intervention data collection periods will cover the same months of the year to avoid any seasonality bias. Women whose caesareans were performed in another hospital and who were subsequently transferred to a participating hospital will be excluded from the study.

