### Assessment criteria

These criteria were measured for a 6-month period (May 2–November 2, 2014) preceding the intervention year and will be measured again in the 6 months following the end of the intervention, corresponding to the same months of the year.

The primary assessment criterion is the NMIC rate.

We conducted a literature review to discern the diagnostic reasoning underlying evidence-based indications for caesareans. The four main indications for caesareans in Burkina Faso are: previous caesarean, prolonged/obstructed labour, pre-eclampsia, and acute foetal distress. In the 22 participating hospitals in the pre-intervention study, these four indications accounted for 76 % of all caesareans performed. The relevant references [47–70] were consulted and used to generate a provisional list of good practice criteria. Preference was given to evidence obtained through randomized controlled trials, considered the most rigorous. The provisional list of criteria was sent to 16 international and national experts (gynecologist-obstetricians, midwives, and a public health physician, see Additional file 10). The experts gave their opinions on the relevance of each criterion and proposed others. The criteria retained were those validated by at least two-thirds of the experts. We then developed clinical decision trees (algorithms) for managing the four main indications for caesareans and derived the criteria for NMIC.

The NMIC criteria are presented in Table 1. For each indication, all the criteria are considered simultaneously. A caesarean is judged to be non-medically indicated when all the criteria are met or when they are not documented and no opposing medical indication is provided. The NMIC rate was calculated for each hospital. This rate is the proportion of NMICs among all the caesareans performed for the four indications during the same period.

**Table 1 Tab1:** Criteria for non-medically indicated caesareans ^a^

Previous caesarean section	Prolonged/obstructed labour

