### Sample size calculation

This is a superiority trial, in which the intervention will be considered effective if it leads to a reduction of at least 50 % in the NMIC rate. The sample size was calculated to maximize statistical power [78]. With an α risk of 5 % (two-sided testing) and 1-β power of 90 %, and a variance inflation factor (VIF) = 3 (calculated using an average of 100 caesareans per hospital and an intra-cluster correlation coefficient (ρ) estimated at 0.02), 2,200 caesarean records and 22 hospitals are needed.

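### The 90% power and 2,200 records assume 100 analysable caesareans per hospital, but the primary endpoint uses only about 76, and no control rate is stated from which the power can be checked

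*Protocol article*

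**What the plan says.** The Sample size calculation section of the protocol article gives these inputs: "With an α risk of 5 % (two-sided testing) and 1-β power of 90" per cent; a target stated as "the intervention will be considered effective if it leads to a reduction of at least 50 % in the NMIC rate"; and "a variance inflation factor (VIF) = 3", "calculated using an average of 100 caesareans per hospital and an intra-cluster correlation coefficient" of 0.02. It concludes that 2,200 caesarean records and 22 hospitals are needed. It states no control-group NMIC rate.

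Under Inclusion and exclusion criteria, records are taken whatever the indication: "The first 100 women with caesarean deliveries in the 6 months following the end of the intervention will also be included". The same rule applied in the pre-intervention period.

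Under Assessment criteria the primary rate has a narrower base: "This rate is the proportion of NMICs among all the caesareans performed for the four indications during the same period". The same section reports the size of that base: "In the 22 participating hospitals in the pre-intervention study, these four indications accounted for" 76% of all caesareans.

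The only NMIC rates quoted are in the Abstract and Background, which give 12 to 24% of caesareans, without restriction to the four indications.

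**The concern.** The cluster size in the power calculation and the denominator of the primary endpoint are different quantities. A record for any other indication is collected but cannot enter the primary rate, so the stated 90% belongs to a larger sample than the endpoint will have.

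Power for a 50% relative reduction also depends heavily on the control rate. Without that rate, a reader can neither reproduce the 90% nor tell which denominator the planning rate was on.

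At stake is a figure the trial relies on. The 90% is the yardstick for reading a null result, and the Analysis strategy section uses it as the reference when it warns of lower power in subgroup analyses.

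**Working it through.** **Inputs.** From Sample size calculation: two-sided α 0.05, power 0.90, 50% reduction, ρ = 0.02, m = 100 per hospital. From the Abstract: 11 hospitals per arm. From Assessment criteria: 76% of caesareans in the endpoint's denominator. Assumed, because not stated: the control rate p1, with p2 = p1/2. The comparison is between arms after the intervention.

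**Step 1. The plan's inflation factor.** VIF = 1 + (m − 1)ρ = 1 + 99 × 0.02 = 2.98, which agrees with 3.

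**Step 2. The plan's 2,200.** n per arm = (1.960 + 1.2816)² × [p1(1 − p1) + p2(1 − p2)] / (p1 − p2)² × 3.

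- 15% to 7.5%: 10.507 × 0.196875 / 0.005625 = 367.8; × 3 = 1,103 per arm, 2,207 in total.
- 12% to 6%: 2,837 in total.
- 24% to 12%: 1,261 in total.

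So 2,200 points to a control rate near 15%; neither end of the quoted range gives it. A pooled-variance formula gives 2,226 at 15%, so the inference does not hang on the choice of formula. Since 22 × 100 = 2,200, the figure covers one period. Both periods together would be 4,400.

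**Step 3. Analysable records.** 0.76 × 100 = 76 per hospital; 22 × 76 = 1,672 per period; 11 × 76 = 836 per arm. VIF = 1 + 75 × 0.02 = 2.5. Effective n per arm is 836 / 2.5 = 334.4, against 1,100 / 2.98 = 369.1 with 100 per hospital. The records fall by 24%, but the effective size falls by only 9%, because smaller clusters are inflated less.

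**Step 4. Power.** Power = Φ(|p1 − p2| / SE − 1.960), with SE = √{[p1(1 − p1) + p2(1 − p2)] / effective n}. At 15%:

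- m = 100: 0.075 / 0.02309 = 3.248, power 90.1%.
- m = 76: 0.075 / 0.02426 = 3.091, power 87.1%.

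The last column replaces the normal reference with a noncentral t on 20 degrees of freedom (22 hospitals less 2).

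| Control rate on the endpoint's denominator | m = 100, z | m = 76, z | m = 76, t |
|---|---|---|---|
| 12% | 81.7% | 77.8% | 73.7% |
| 15% | 90.1% | 87.1% | 83.6% |
| 18% | 95.0% | 93.0% | 90.4% |
| 24% | 99.0% | 98.3% | 97.3% |

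With 76 per hospital, power reaches 90% at a control rate of about 16.3% by this z formula and about 17.8% by t.

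**Step 5. What the denominator alone costs.** Four formulas were tried: pooled z, unpooled z, log odds ratio Wald, and t. For each, the control rate was set so that power is exactly 90% at m = 100 (rates of 15.0 to 16.3%). Moving to m = 76 then gives 87.0% every time, a loss of about 3 points.

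**Step 6. If the planning rate is a share of all caesareans.** Suppose also that every NMIC falls within the four indications. The rate on the restricted denominator is then the quoted rate divided by 0.76.

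- 12% / 0.76 = 15.8%: power with 76 per hospital is 88.9% (z) or 85.7% (t).
- 15% / 0.76 = 19.7%: power is 95.2% (z) or 93.2% (t).

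**The case against.** The strongest reply is that cutting the cluster to 76 while leaving the rate unchanged mixes two denominators. The 12–24% is quoted for caesareans in general. If all NMICs lie within the four indications, the restriction raises the rate as it shrinks the sample, and power goes up: at 12%, from 81.7% with 100 per hospital to 88.9%. This stands as a possibility. The documents do not say which denominator the planning rate used, nor whether NMICs occur outside the four indications, so the direction of the error is not settled.

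A reader might infer that the design delivers only 84–87% power, or 74–78% at the low end. The documents do not support that as a flat statement, for three reasons:

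- The 15% behind 84–87% is back-solved and appears nowhere in the article.
- The 84% and 74% add a t reference, whereas Analysis strategy specifies a Wald test from generalized estimating equations. With 22 hospitals that is a fair caution, but it is a separate one and lowers power at 100 per hospital too.
- At 12%, most of the shortfall comes from the low rate, since power is already about 82% with 100 per hospital.

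Two further points limit precision. The Abstract names the change in rate as the main criterion, and use of pre-intervention data could alter power, but the correlation needed to quantify this is not given. The Abstract also speaks of every caesarean patient in each six-month period rather than the first 100; on that reading clusters could be larger.

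Finally, a condensed article may leave the control rate to the full protocol. That answers the missing rate in part. It does not answer the mismatch between the stated cluster size and the stated endpoint, both of which are in the article.

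**Conclusion.** The mismatch holds on the text alone: the calculation counts 100 caesareans per hospital and the endpoint uses about 76. The 90% is therefore not established for the endpoint as defined, and cannot be reproduced without supplying a control rate.

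The size is modest and conditional. It is about 3 points (90% to 87%) if roughly 15% was assumed on the four-indication denominator. Over 12–24% on that denominator, power runs from about 78% to 98% by z, or 74% to 97% by t. If the quoted range is a share of all caesareans and all NMICs fall within the four indications, power at the low end is about 86–89%, and planning rates moderately above 12% keep it above 90%.

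These figures assume ρ = 0.02, 76 analysable records in every hospital, and a post-intervention comparison. It would go too far to conclude that the trial is seriously underpowered or needs more patients. The supportable conclusion is that a relied-upon figure was computed on the wrong count and lacks its key input.

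**What to change.** Restate the Sample size calculation section as follows:

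- Use about 76 four-indication caesareans per hospital and a variance inflation factor of 2.5 at ρ = 0.02.
- State the control NMIC rate and say that it is on the four-indication denominator. Assessment criteria says the rate was calculated for each hospital, and the pre-intervention data are in hand, so the observed rate and an intra-cluster correlation estimated from those data can replace assumed values.
- Say that 2,200 is the number of records in one period, of which about 1,672 enter the primary rate.
- Report the power that results in place of 90%, with a short range over plausible control rates. If a small-sample reference is used, show its effect separately.

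The text should not fix 84% or 74% as the power, since both rest on an undocumented rate and an added t correction.

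The cost is a change of wording. Hospitals, endpoint, test and record collection stay as they are, and no more patients are needed. The downside is that the stated power may become slightly less favourable.

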### Analysis strategy

For evaluating the effectiveness of clinical audits in reducing NMIC rates, the unit of analysis is the patient. The main tests will be intention-to-treat analyses. A first descriptive analysis will be done to verify group comparability in terms of the characteristics of hospitals and patients included in the pre-intervention period. The primary analyses will take into account inter- and intra-cluster variability. We will use generalized estimating equations (GEE) to adjust the variance estimation for the intervention’s effect on inter-dependence of the measured events (NMIC or not) among patients of the same hospital [79]. The exchangeable structure of the residual covariance matrix will be used to represent the intra-cluster correlations. The same approach will be used to test the effectiveness of CBCAs in relation to resource improvement (complexity score), medical practices (caesarean quality score), and reductions in maternal and perinatal mortality. The intervention’s effect on the NMIC rate will be estimated from the odds ratio (95 % CI) based on the GEE approach and tested with the two-sided Wald test (α = 0.05) [79]. The intervention’s effects will be evaluated systematically both without adjustment and with adjustments on the stratification variables (type of hospital) and on the other baseline characteristics selected a priori, whose distribution could, even with randomization, be unbalanced between the two groups.

Preliminary analyses will test whether the intervention’s effects vary according to hospital type, using chi-squared likelihood ratio tests with 2 degrees of freedom for hospital–intervention interaction. If the test does not reject the null hypothesis with α = 0.05, the interactions will be eliminated from the final model, which will enable the overall effect of the intervention to be estimated. However, if the interactions are statistically significant, subgroup analyses will be done to estimate the effects of the intervention separately for each type of hospital (district vs. regional), with a power of less than 90 %. A similar approach will be used to test whether the intervention’s effects depend on: 1) the caesarean rate in the pre-intervention period; 2) the initial knowledge score in the pre-intervention period; or 3) patient characteristics (age, parity, previous caesarean, prenatal care, referral for delivery) and any other variables distributed unevenly among groups in the pre-intervention period. In all secondary analyses, the intervention’s effects will be estimated from the adjusted odds ratio using the GEE approach, which generalizes the logistic regression to clustered data [79]. To analyze the implementation and heterogeneity of effects, interviews will be fully transcribed into a word processor program. Subsequently, qualitative data will be coded and organized using QDA Miner software and then subjected to content analysis [80].

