## Background

In Burkina Faso, although the national caesarean rate increased from 0.7 % in 2003 [1] to 2 % in 2010 [2], it remains well below the minimum rate of 3 % required to meet the needs [3]. The institutional caesarean rate has risen steadily since the introduction of a policy to subsidize emergency obstetric care in 2006, which significantly increased access to caesareans [4]. Under this policy, caesarean costs are subsidized up to 80 % (100 % in some districts) and transportation is fully funded between primary health centres and referral hospitals, where caesareans are performed. Similar policies have led to very high institutional caesarean rates in other sub-Saharan countries [5]. In fact, according to Burkina Faso’s Ministry of Health, the rate surpassed 40 % in some hospitals in 2013 [6]. Research has shown, however, that between 12 and 24 % of caesareans in that country are not medically indicated [7, 8].

In Burkina Faso, as in many African countries, excessive caesarean rates in some hospitals have been attributed to limited training and knowledge of personnel [7, 9]. In those facilities, it is not only obstetricians who assess indications for caesareans, but also general practitioners and nurses trained in emergency surgery (a 6-month training program involving 1 month of theoretical courses and a 5-month practicum in surgical and obstetric emergencies).

While greater access to caesareans is a necessity in countries where the national rate is below 10 % [10], it is imperative that quality improvement programs be implemented at the same time to prevent excessive and inappropriate increases in caesarean rates [11]. High rates of non-medically indicated caesareans (NMIC) are associated not only with adverse health outcomes for mothers and infants, but also with high public spending on health, presenting equity and efficiency challenges for low-resource countries [12–19].

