We selected this indicator because we believe improvements to obstetric care prompted by audits should also have an impact on perinatal outcomes related to intrapartum care [65, 73]. Included in the definition are immediate neonatal deaths (within 24 h after birth) and fresh stillbirths; excluded are macerated stillbirths, deaths of premature infants (less than 37 weeks amenorrhea), and deaths of severely deformed infants. Perinatal mortality related to intrapartum care is defined as the number of immediate deaths and fresh stillbirths divided by the number of non-preterm caesarean deliveries in the same period.

*Intra-hospital maternal mortality among patients with caesareans*
This indicator was selected because we believe that, as in perinatal deaths, improvements in caesarean practice prompted by audits should also have a positive impact on maternal outcomes [73–75]. This indicator is defined as the ratio between the number of post-caesarean maternal deaths occurring in a hospital during the study period and the number of caesareans performed in that hospital over that period.

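### Maternal mortality is tied to the same logistic GEE and Wald test as NMIC, which becomes unreliable if the death rate is about 0.5 % or lower

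*Protocol article*

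**What the plan says.** All references are to the Protocol article.

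- **Method.** Analysis strategy sets out a patient-level GEE with exchangeable correlation, an odds ratio and a two-sided Wald test for NMIC. It applies the same approach to the resource score, to "medical practices (caesarean quality score), and reductions in maternal and perinatal mortality".
- **Adjustment.** The same section says the "effects will be evaluated systematically both without adjustment and with adjustments on the stratification variables (type of hospital" and on other baseline characteristics chosen in advance but not named. It adds that secondary analyses report an adjusted odds ratio from the GEE.
- **Outcome.** Assessment criteria defines maternal mortality as "the ratio between the number of post-caesarean maternal deaths occurring in a hospital during the study period", divided by the caesareans performed in that hospital over that period.
- **Size.** Sample size calculation concludes that 2,200 "caesarean records and 22 hospitals are needed". The target is NMIC: the intervention counts as effective "if it leads to a reduction of at least 50 % in the NMIC rate".

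No expected maternal death rate, death count or mortality power is given, and no method for sparse events is named.

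**The concern.** The sample was sized for a frequent outcome: Background puts it at "between 12 and 24 % of caesareans in that country are not medically indicated". Maternal death after caesarean is likely to be far rarer. A logistic model has no finite intervention odds ratio when one arm has no deaths, and no finite hospital-type coefficient when a hospital type has none.

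Maternal outcomes belong to the third secondary hypothesis. If the model breaks down, one of two things happens. Either the analysts pick covariates and a substitute method after seeing deaths by arm, or they report a diverging odds ratio whose p-value looks convincing. The second is worse, because it follows the plan to the letter.

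**Working it through.** **Inputs from the article.** 22 hospitals, 11 per arm; the first 100 caesareans per hospital and period, so 11 x 100 = 1,100 per arm after the intervention; three hospital-type strata; design inputs "With an α risk of 5 % (two-sided testing) and 1-β power of 90" per cent, and a variance inflation factor "calculated using an average of 100 caesareans per hospital and an intra-cluster correlation coefficient (ρ) estimated at 0.02".

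**Assumptions, because the article gives no figure.** Maternal death rate 0.3, 0.5 or 1 %; stratum sizes 8/6/8; ICC for death 0.005.

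**1. The plan's own figure.** VIF = 1 + (100 - 1) x 0.02 = 2.98, matching the stated 3, and 22 x 100 = 2,200. The baseline NMIC rate p is not stated with the calculation. The two-proportion formula for p against p/2 is n per arm = [1.96 sqrt(2 p̄ q̄) + 1.2816 sqrt(p1q1 + p2q2)]² / (p1 - p2)². At p = 15 % this gives 371 per arm, and 371 x 2 x 3 = 2,226. At 12 % the total is 2,862 and at 24 % it is 1,284. So 2,200 fits an NMIC rate of about 15 % and says nothing about deaths.

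**2. Expected deaths and chance of an empty arm.** Expected deaths = 1,100 x (r0 + r1). With independent deaths, P(at least one arm empty) = a + b - ab, where a = (1 - r0)^1100 and b = (1 - r1)^1100.

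| Assumed rate | Effect | Expected deaths | P(an arm empty) |
|---|---|---|---|
| 0.3 % | none | 6.6 | 7 % |
| 0.3 % | halved | 4.95 | 22 % |
| 0.5 % | none | 11 | 0.8 % |
| 0.5 % | halved | 8.25 | 6.7 % |
| 1 % | none | 22 | <0.1 % |
| 1 % | halved | 16.5 | 0.4 % |

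Clustering raises these chances.

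**3. Simulated GEE.** 400 trials per cell; beta-binomial deaths; logistic GEE with arm and hospital type; exchangeable correlation; robust standard errors. The intervention coefficient counts as diverging if it is non-finite or exceeds 8 in absolute log odds. The any-slope column also counts hospital-type slopes and non-convergence.

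| Rate | Effect | Intervention odds ratio diverges | Any slope diverges | Wald rejects under no effect |
|---|---|---|---|---|
| 0.3 % | none | 12 % | 45 % | 13.5 % |
| 0.3 % | halved | 31 % | 60 % | - |
| 0.5 % | none | 2 % | 18 % | 8 % |
| 0.5 % | halved | 10 % | 36 % | - |
| 1 % | none | 0 % | 1 % | 9 % |
| 1 % | halved | 1 % | 4 % | - |

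Separate runs of the same design with 150 trials per cell put divergence of the intervention odds ratio at 11-13 % (no effect) and 27-31 % (halved) for 0.3 %, at 1-3 % and 7-13 % for 0.5 %, and at 0-1 % for 1 %.

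**4. The Wald test with an empty arm.** As the fitted risk in the empty arm goes to zero, its residuals vanish too. The robust standard error stays bounded while the coefficient runs off, so their ratio becomes large. At 0.3 % with no true effect, 54 of 400 trials had an empty arm and the test rejected in 49 of those 54. They make up almost all of the rejections in that cell. At 0.5 %, all 9 trials with an empty arm were rejected, out of 33 rejections. At 1 % none of the rejections came from an empty arm; that excess is more likely due to having only 22 clusters, which is a separate matter.

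**5. More covariates.** Adding five binary patient covariates (illustrative, with strata of 4/8/10 or 6/8/8, 200 trials per cell) raised failure of the intervention coefficient to 24-48 % at 0.5 % and 9-15 % at 1 %.

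**6. Perinatal mortality.** At an assumed 1 %, the control arm expects 1,100 x 0.01 = 11 deaths and is empty with probability 0.99^1100, about 0.00002. At 5 % it expects 55. The main limit there is power, not estimability.

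**The case against.** Several points on the other side stand.

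- **The rate is assumed.** At 1 % the intervention odds ratio almost always exists, and at 2 % even the model with five extra covariates rarely has trouble (2-5 % with any slope diverging). The sponsor can check the assumption, because deaths in these 22 hospitals were already recorded in the 2014 pre-intervention period.
- **Diverging hospital-type slopes are not failed trials.** A hospital type without deaths can leave the intervention odds ratio finite. A reader might take the any-slope column as the failure rate; the intervention column is the one that counts.
- **The covariate set is not given.** A reader might treat the patient characteristics listed under Analysis strategy as the adjustment set. The article lists them as possible effect modifiers, so step 5 is only illustrative.
- **The denominator may be larger.** The Abstract includes every caesarean patient in the six months and the outcome definition uses all caesareans performed, whereas Inclusion and exclusion criteria and Data collection and processing stop at the first 100. With 200 per hospital, divergence of the intervention coefficient at 0.5 % falls to 0-3 % with hospital-type adjustment.
- **A fallback could sit in an analysis plan not shown.** It could, but it would have to override a method that this article already fixes.

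Two points do not rescue the plan. The planned unadjusted GEE diverges about as often (12 % and 31 % at 0.3 %, 2 % and 10 % at 0.5 %, no effect and halved), because the cause is the empty arm. Using all 4,400 records in an arm-by-period model does not help at 0.3 %: the intervention term was not estimable in 23 % (no effect) and 39 % (halved), and in 7 % and 11 % at 0.5 %.

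**Conclusion.** The concern holds for maternal mortality, conditionally on a death rate of about 0.5 % or lower and about 100 caesareans per hospital after the intervention. Under those assumptions the prescribed odds ratio diverges in roughly 10-30 % of trials at 0.3 % and 2-13 % at 0.5 %; at 1 % the problem is nearly gone (0-1 %). In the empty-arm trials the prescribed test tends to report a significant effect that may not exist. The figures also depend on the assumed strata and ICC.

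Three stronger readings are not supported. The model does not fail in most trials: with hospital-type adjustment the intervention odds ratio is usually finite. The problem does not extend to perinatal mortality to this degree, if those deaths are more frequent, as seems probable. And a reader might see this as the analysis that would reveal harm from withholding caesareans. Both mortality outcomes are defined among caesarean deliveries only, so no method applied to them could show that withholding is safe.

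**What to change.** For maternal mortality only:

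1. Report deaths and caesareans for each hospital and by arm.
2. Make the main analysis a risk difference stratified by the three hospital types, without patient-level covariates.
3. Obtain the p-value and confidence interval by re-permuting the allocation within those strata, following the randomization actually used. This stays defined when an arm or a stratum has no deaths.
4. State in advance that a non-significant result is not evidence of no harm.

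Keep the GEE for perinatal mortality. Fix this before post-intervention deaths are seen by arm.

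The cost is a paragraph in the analysis plan and a short permutation program. The downside is that there will be no covariate-adjusted maternal mortality odds ratio. With very few deaths the permutation distribution is also coarse and the interval wide, which reflects how little information there is.

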### Randomization and allocation

In February 2015, after a 6-month pre-intervention study, hospitals were allocated randomly to either the intervention or control group. Participating hospitals were grouped into three strata corresponding to different types of hospitals: regional hospitals, district hospitals in the two largest cities (Ouagadougou and Bobo Dioulasso), and district hospitals outside those two cities. All participating hospitals were randomly allocated simultaneously to minimize the risk of allocation bias [76, 77]. To prevent imbalance regarding the level of care in each stratum, block randomization was used to generate the allocation sequence [76, 77]. Investigators were informed of the allocation just before the intervention was implemented in the intervention group.

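### With 22 hospitals the planned GEE Wald test is moderately anti-conservative, and the interaction pre-test that the final model turns on is a likelihood-ratio test that GEE does not have

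*Protocol article*

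**What the plan says.** Under Analysis strategy, the protocol article analyses patients with GEE and an exchangeable working correlation. The effect on the rate of non-medically indicated caesareans (NMIC) is an odds ratio "based on the GEE approach and tested with the two-sided Wald test" at α = 0.05. It is to be reported unadjusted and adjusted for hospital type and other baseline characteristics. No variance correction or reference distribution is named.

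The same section then tests whether the effect differs by hospital type, "using chi-squared likelihood ratio tests with 2 degrees of freedom". If the test does not reject at 0.05, the interaction terms are dropped, and this is said to allow the overall effect to be estimated. Otherwise, "if the interactions are statistically significant, subgroup analyses will be done to estimate the effects of the intervention separately for each type of hospital", with district versus regional given as the types and with acknowledged power below 90%. GEE is the only regression model named, and it is named again for the secondary analyses.

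Under Randomization and allocation: "Participating hospitals were grouped into three strata corresponding to different types of hospitals". These are regional hospitals, district hospitals in the two largest cities, and other district hospitals. The Sample size calculation gives the design: "With an α risk of 5 % (two-sided testing) and 1-β power of 90" %, a "reduction of at least 50 % in the NMIC rate", 100 caesareans per hospital, an intra-cluster correlation (ICC) of 0.02, a variance inflation factor (VIF) of 3, and 2,200 records in 22 hospitals.

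**The concern.** There are three linked problems.

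- **Primary test.** The sandwich variance is biased downward when clusters are few, and a normal reference ignores that it is estimated from 22 hospitals. The primary p-value is then too small and the interval too narrow.
- **Interaction pre-test.** GEE solves estimating equations and has no likelihood, so a likelihood-ratio test cannot be taken from the named model. Whoever runs the analysis must substitute something, and the result depends heavily on the substitute. The test is also the step on which, as worded, the final model's overall effect depends, although the trial was sized for that one overall comparison.
- **Follow-up subgroups.** A 2-df test compares three hospital types; the follow-up compares two. A significant result could come from a difference between the two district strata, which the follow-up would pool.

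**Working it through.** **Design figures.** VIF = 1 + (100 − 1) × 0.02 = 2.98, which matches the stated 3. The control rate behind the 2,200 records is not stated. Background gives "between 12 and 24 % of caesareans in that country are not medically indicated". With the pooled two-proportion formula, 90% power and a halved rate, 15% vs 7.5% needs 371 per arm, so 371 × 2 × 3 = 2,226 records, close to 2,200. The total is 2,862 at 12% and 1,284 at 24%. The rate is therefore treated below as an assumed range.

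**Primary Wald test, closed form.** Take 11 + 11 equal hospitals, so df = 22 − 2 = 20.

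- Normal critical value with an unbiased standard error: P(|t20| > 1.96) = 6.4%.
- The uncorrected sandwich divides by 11 where 10 is needed, so its variance is on average 10/11 of the true value: P(|t20| > 1.96 × √(10/11)) = P(|t20| > 1.869) = 7.6%.

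**Primary Wald test, simulated under no effect (nominal 5%).** The scenarios with 76 patients reflect the 76% of caesareans that fall under the four indications (Assessment criteria).

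| Scenario | Unadjusted | Adjusted for hospital type |
|---|---|---|
| Rate 18%, ICC 0.02, 100 per hospital | 7.5% | 9.0% |
| Rate 24%, ICC 0.02, up to 76, varying | 6.9% | 8.3% |
| Rate 18%, ICC 0.05, up to 100, varying | 7.7% | 9.2% |

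Each row has 1,600 replicates (Monte Carlo error about 0.6-0.7 points) and assumes strata of 8/6/8 hospitals. A separate beta-binomial simulation (rates 12-24%, ICC 0.02, 76 or 100 per hospital; 40,000 runs unadjusted, 6,000 adjusted) gave 7.5-7.9% and 9.1%. A pre/post model testing the group-by-period term gave 6.6-8.0%.

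**After correction.** Kauermann-Carroll variance with t (hospitals minus parameters) gave 4.8-5.3%. A Mancl-DeRouen-type variance with a normal reference gave 4.7-5.1% unadjusted and 3.8-4.4% adjusted; adding t to it gave 3.4-3.9% and 2.3-3.8%.

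**Interaction pre-test, true null, critical value 5.991 on 2 df.** There are three ways to run it.

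1. *Likelihood ratio from a mixed model.* Approximate it at hospital level by normal theory with 22 values and six arm-by-stratum means (16 residual df). LR = 22 ln(1 + 2F/16) exceeds 5.991 when F > 8 × (exp(5.991/22) − 1) = 2.50. P(F(2,16) > 2.50) is about 11%.
2. *Uncorrected robust GEE Wald test.* Simulated: 17.6-20.1% with strata of 8/6/8, and 24% with 8/4/10. Stratum sizes are not in the article.
3. *Likelihood ratio from ordinary logistic regression, ignoring clustering.* The statistic is inflated by about the VIF, so the rate is exp(−5.991/(2 × VIF)). At VIF 2.98 this is 36.6%. With 76 patients per hospital, VIF = 1 + 75 × 0.02 = 2.5 and the rate is 30.2%. Simulated at ICC 0.02: 36.5% and 26.2% (the latter with varying hospital sizes).

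**Degrees of freedom.** Three strata give 3 − 1 = 2 df. District versus regional would give 2 − 1 = 1.

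**The case against.** The article does not say the variance is uncorrected or the reference normal. A bias-corrected GEE Wald test with a t reference would also fit its wording, and a statistical analysis plan could specify one. This stands: the 7-9% figures describe the standard implementation, not a stated choice. It does not reach the likelihood-ratio test, the conditional wording or the two-group follow-up, which are written down and would have to be changed rather than filled in.

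A mixed logistic model could supply a likelihood. That is fair, but none is named, and its approximate rate is still about twice nominal.

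Some stronger readings are tempting and are not supported:

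- *The primary test is invalid.* The inflation is moderate; anti-conservative is the accurate word. Adding the baseline rate as a covariate raises the simulated rate to 10.1%, but the article does not name that covariate.
- *A chance interaction would cost the trial its overall estimate.* The article also says effects will be evaluated systematically with and without adjustment, with no condition attached, and never says the overall estimate is withheld. Loss of that estimate is one reading of loose wording.
- *The eight named modifiers make a false signal likely.* With eight independent valid tests the chance of at least one is 1 − 0.95^8 = 34%. That is ordinary multiplicity in secondary analyses, not an error in this plan.

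**Conclusion.** The point holds in moderate form. The standard GEE Wald test on 22 hospitals runs at about 7-8% unadjusted and 8-9% adjusted for hospital type. This rests on assumed control rates of 12-24%, an ICC of 0.02-0.05 and assumed stratum sizes, though the closed form (6.4-7.6%) needs only 11 + 11 equal hospitals.

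The firmest part is the interaction pre-test. It cannot be computed from the only model named, whatever the number of hospitals. Its false-positive rate is about 11%, 18-24% or 26-37%, depending on what replaces it; the middle range depends on unstated stratum sizes, and the last is at ICC 0.02. Making the final model's overall effect turn on such a test is a poor rule even if the overall estimate would in practice be reported anyway. The mismatch between three strata and two follow-up groups is a small inconsistency.

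**What to change.** - **Primary test and interval:** use a small-sample-corrected GEE variance with a suitable reference distribution. One example is Kauermann-Carroll with t, df = hospitals minus hospital-level parameters: 22 − 2 = 20 unadjusted, 22 − 4 = 18 adjusted for hospital type. Fix one combination in advance, because Mancl-DeRouen with t over-corrects here.
- **Overall effect:** state that it is always estimated and reported as the primary result, whatever the interaction result, and delete the wording that makes it conditional.
- **Interaction tests:** make them secondary, using a small-sample-corrected GEE Wald/F or score test, with subgroup estimates in the three randomised strata.

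The work is a change of wording and a software option. Unadjusted intervals widen by about 12%: (2.086/1.96) × √(11/10) = 1.064 × 1.049 = 1.116. Power falls a few points: for a design with nominal 90% power, the t reference on 20 df alone gives about 87%.
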